## Abstract

**Background:**

Eating disorders (EDs) are serious disorders that significantly affect not only the lives of patients, but also those of their family members who often experience high levels of burden, suffering and helplessness. If, in addition to ED, the patient has a personality disorder (PD), the psychological distress experienced by family members can be devastating. However, few treatments have been developed for family members of people with ED and PD. Family Connections (FC) is a programme that has been shown to be effective for family members of people with borderline personality disorder. The overall aims of this work are: (a) to adapt FC for application to family members of patients with BPD-PD (FC: ED-PD); (b) to analyse, in a randomised controlled clinical trial, the efficacy of this programme in a Spanish population, compared to a control condition consisting of treatment as usual optimised treatment (TAU-O); (c) to analyse the feasibility of the intervention protocol; (d) to analyse whether the changes that may occur in relatives are related to improvements in the family climate and/or improvements observed in patients; and (e) to analyse the perceptions and opinions of relatives and patients about the two intervention protocols.

**Methods:**

The study uses a two-arm randomised controlled clinical trial with two experimental conditions: adaptation of FC programme (FC: ED-PD) or Treatment as usual optimised (TAU-O). Participants will be family members of patients who meet DSM-5 criteria for ED and PD or dysfunctional personality traits. Participants will be assessed before and after treatment and at one-year follow-up. The intention-to-treat principle will be used when analysing the data.

**Discussion:**

The results obtained are expected to confirm the effectiveness of the programme and its good acceptance by family members.

*Trial registration* ClinicalTrials.gov Identifier: NCT05404035. Accepted: May 2022.

## Background

Eating disorders (ED) produce significant disturbances related to food intake, and they often result in intense preoccupation with weight and the figure, as well as the use of control strategies such as dieting and purging [1]. In severe cases or without adequate treatment, ED can affect the body’s organs [2] and the individual’s social functioning, and they are associated with psychological problems such as depression, anxiety, social isolation, family conflicts, low self-esteem, a negative self-concept, and reduced autonomy [3].

A diagnosis of an ED is a burden for families or primary caregivers (usually mothers) that impacts their daily lives. Caregivers of patients with ED commonly experience mental health problems, psychological distress, and burden due to their caregiving experiences, which affects their mental health, quality of life, and well-being [4–6]. Caregivers frequently express the need for information about how to help their loved one with ED recover from the disorder [7]. Thus, it is necessary to include family members in treatment programs that offer support and psychoeducation [8].

So far, there are three types of empirically supported interventions for family members of people with eating disorders: (a) psychoeducational interventions [8–11], (b) interventions based on systemic cognitive behavioural therapy [12–14], and (c) interventions based on the New Maudsley Model [15–22].

Sepúlveda et al. [23] conducted the first RCT with Spanish ED caregivers to study the effectiveness of The Collaborative Care Skills Workshop program by comparing it with a psychoeducational group program containing six two-hour sessions based on Fairburn’s [24] program. Patients were receiving parallel CBT for ED. The results indicated that, although there were no statistically significant differences between the two experimental conditions, after treatment there was an improvement in the relatives’ perception of illness, adaptation to ED symptoms, perceptions of themselves as caregivers, and level of distress. However, no statistically significant differences were found between before and after treatment in the level of expressed emotion, emotional over-involvement, critical comments, family adaptation to the disorder, anxiety, depression, self-efficacy, experience of caring, or impact of ED symptoms on family members. Regarding the patients, there was a reduction in their symptoms of ED and psychological distress after the intervention, but it was not maintained at follow-up. Sepúlveda et al. [23] suggested that six sessions could be insufficient to find changes after treatment. In addition, it should be noted that the patients who participated had a long duration of the problem and were resistant to treatment, and although it was not evaluated, they might have had a comorbid personality disorder.

In summary, there is scientific evidence supporting the efficacy of interventions specifically designed to help caregivers of people with ED. All these programs focus on providing caregivers with knowledge about the functioning of the disease and strategies to provide adequate support for their loved ones while attending to their own needs. Overall, the results showed significant decreases in caregivers’ experienced burden, distress, anxious and depressive symptomatology, expressed emotion, and symptom accommodation behaviors. Likewise, there was a significant increase in self-efficacy, general well-being, and knowledge and skills in relating with their loved ones. In addition, some of the studies [10, 14, 16, 21, 23] also evaluated the effects of the program on the patients, generally reporting improvements in the progression of the disorder and a reduction in symptomatology. However, these results were not maintained at the follow-ups.

Some of the most important transdiagnostic symptoms of ED (impulsivity, emotional dysregulation, intolerance to emotions, and interpersonal problems) [25] are characteristic of Borderline Personality Disorder (BPD). This comorbidity involves a high frequency of binge eating, purging, difficulties in interpersonal relationships, risk of self-harm and suicide, non-adherence to treatment, and non-compliance with therapeutic tasks, all of which increases the risk of chronicity [26, 27]

Guillen et al. [28] conducted an intervention based on the principles of Dialectical Behavior Therapy (DBT) [29] with 115 family members of patients with a diagnosis of ED and PD who were undergoing treatment in a specialized unit. The intervention took place face-to-face and in groups, and it consisted of eight weekly sessions. The intervention modules were: psychoeducation about ED and PD, description of the emotional dysregulation model of PD, validation techniques, radical acceptance techniques, knowing the limits in the family environment, and learning to manage the characteristic problems of ED and PD (binge eating, vomiting, self-harm, suicidal behaviors, emotional outbursts, substance abuse, and relapses). The intervention was shown to be effective in reducing burden and increasing caregiver self-efficacy. Although results from this study can be considered preliminary because there was no control group, the results indicate that it is possible to help caregivers of people with ED and PD.

Psychoeducation groups for relatives of people diagnosed with BPD provide information about the illness and, thus, help them to understand some of the behaviors of their family members, in order to improve the relationship and family coexistence [30–33]. Fruzzetti’s group developed and tested the program *Family connections: A program for relatives of persons with Borderline Personality Disorder* (FC) [34], which is designed to be delivered either by professionals or by relatives who have previously completed a training course. The FC program contains 12 two-hour weekly sessions. The content of the intervention program is divided into six modules and includes: psychoeducation about BPD, how it affects family functioning, skills adapted from DBT [29] (individual, family, and relational skills, validation exercises, and problem-solving skills), and peer support. All the modules include specific practical exercises and homework assignments. In addition, throughout the FC program, there is a forum where participants can build a support network. To test the efficacy of FC, five uncontrolled clinical trials have been conducted so far, with pre-post evaluation moments and follow-ups [34–38]. The results of these five studies show significant decreases in family members’ subjective experience of illness burden, perceived distress, depression, and grief, as well as improved coping strategies. These changes were maintained at the three-month follow-up.

Despite the results from programs focused on the specific symptoms of ED, mentioned above, the studies did not report information about comorbid diagnoses, presence of self-harm, suicidal behaviors, or participants’ diagnosis of PD. Therefore, interventions with caregivers on these common symptoms, which are frequently transdiagnostic, have not been contemplated. Taking into account the high comorbidity observed in ED patients, it would be necessary to evaluate, diagnose, and adapt family support programs to include specific modules that help relatives to cope with the relationship with the patient, in addition to the specific symptoms of ED. Although one of the main objectives of the programs is to improve expressed emotion, none of these studies evaluated or focused on caregivers’ emotional regulation skills. Finally, these programs do not address the management of negative emotions stemming from grief about caring for a person with ED, and they do not usually assess caregivers’ quality of life. Thus, an adaptation of the Family Connections program for relatives of patients with an ED diagnosis would be highly beneficial.

### Objectives and hypotheses

The general objectives of this research project are: (1) to adapt and test the modules of the FC intervention protocol designed specifically for family members of patients with ED-PD in the Spanish population (FC: ED-PD); (2) to analyze, in a randomized controlled trial, the efficacy of the FC: ED-PD program, versus a control condition consisting of optimized treatment as usual (TAU-O), in reducing objective and subjective illness burden, possible clinical symptomatology, and hostility or emotional discomfort, as well as improving family climate and quality of life. The TAU-O control condition will consist of the usual treatment that each family member receives/chooses, depending on their situation, plus a psychoeducation component about ED; (3) to analyze the feasibility and acceptability of this intervention protocol in relatives of patients with ED-PD in a pilot feasibility study that takes different aspects into account: from acceptance by the participants through the consideration of legal and technical aspects, as well as the preparation and implementation of the intervention; (4) to analyze whether the changes that may occur in family members with respect to disease burden and clinical symptomatology are related to improvements in the family climate and/or improvements observed in the patients with ED-PD; and (5) to analyze the perceptions and opinions of families and patients about the two intervention protocols.

The general initial hypothesis, based on the results obtained by Guillén et al. [28] with relatives of patients with ED-PD and those obtained by Fruzzetti’s group in the population with PD [34, 36, 37, 39], is that the FC program designed and developed by Fruzzetti’s group will be effective (both statistically and clinically), compared to optimized treatment as usual (TAU-O), and efficient. The following specific hypotheses are proposed: (1) The FC: ED-PD protocol will be viable, i.e., it can be administered to relatives of patients with ED-PD in clinical centers, both in the National Health System and in private centers, and it will be well accepted by relatives, patients, and clinicians. (2) The FC: ED-PD protocol condition will be more effective than the control condition, which uses the optimized treatment as usual (TAU-O) participants may receive depending on their situation, but optimized with a specific psychoeducation component on ED-PD and its repercussions. (3) Family members, patients, and clinicians will rate the FC: ED-PD protocol significantly higher than the TAU-O control protocol. (4) The improvements that may occur in family members with respect to disease burden and clinical symptomatology will be related to improvements observed in patients with ED-PD and in the perceived family climate.

Attending to and training family members of patients with ED-PD in the different skills required to effectively manage these patients, both in daily life and in times of crisis, will help to alleviate the stress and burden that family members experience on a daily basis. This, in turn, will help to improve family relationships and patient outcomes.

The assessment of the program’s effectiveness for participants will be determined by their differential scores before versus after the application of the interventions and at the 12-month follow-up on the evaluation instruments used. Specifically, we expect: (a) a decrease in scores on variables measuring clinical symptomatology and disease burden (objective and perceived); (b) less interference of the problem in the lives of family members; (c) an improvement in perceived family climate; (d) decreased hopelessness; (e) improved coping strategies; (f) increased quality of life scores; (g) reduced intrafamily conflict; and (h) fewer visits to hospital emergency rooms and fewer emotional and behavioral outbursts by the patient.

The evaluation of the efficiency of the program will be determined by: (a) the ratio of family members who are offered the chance to participate in the program, compared to those who agree to participate; (b) the dropout rate of family members; (c) the evaluation of the program by family members who participate; (d) the evaluation of the program by clinicians who are introduced to the program and the demonstration of its feasibility; and (e) the evaluation of the program by clinicians who participate in the program and the demonstration of its feasibility. In this article, we present the study protocol.

## Methods

### Participants

The sample will be composed of relatives of patients who meet DSM-V criteria (1) for Anorexia Nervosa (both restricting and purging subtypes), Bulimia Nervosa, Binge Eating Disorder, Eating or Food Intake Disorder Not Otherwise Specified, and any PD (or PD traits). The diagnoses will be carried out by a specialist in clinical psychology or psychiatry, and the sample will be recruited in different clinical services: the University Clinical Hospital of Valencia and its Mental Health Reference Units; and the Eating Disorders and Personality Disorders Unit PREVI-ITA and its three centers in Castellón, Valencia, and Alicante.

In the case of the patients, the following inclusion and exclusion criteria will be established: 1) meet the diagnostic criteria for ED and PD (or PD traits); 2) agree to participate in the study in writing by signing the informed consent form; in the case of minors, the consent must be signed by their parents; 3) The presence of another serious pathology such as psychosis, schizophrenia, intellectual disability, etc., will be an exclusion criterion.

In the case of family members, the following inclusion and exclusion criteria will be followed: (1) being a family member of one of the patients with a diagnosis of ED and PD (or PD traits); (2) signing the informed consent; (3) The presence of any pathology in the family member that keeps the intervention from being carried out (such as psychosis, schizophrenia, intellectual disability, substance dependence, etc.) will be an exclusion criterion.

### Study design

First, a pilot feasibility study will be carried out using focus groups to explore the opinions of relatives of ED-PD patients. Semi-structured interviews will be used. The research design will follow the criteria established by Cooke et al. [40], and for the development of the focus groups, the guide developed by Breen [41] for this type of methodology will be used. Second, a randomized controlled clinical trial will be conducted following the CONSORT (Consolidated Standards of Reporting Trials) guidelines http://www.consort-statement.org/ [42, 43]. This study is a superiority trial. The study design consists of a two-arm randomized controlled trial (RCT). On the one hand, there will be two conditions: Family Connections (FC-ED—PD) or Treatment as usual optimized (TAU-O), and family members will be randomized to one of the two groups. -A between-subjects design will be used with three assessment points: pre-treatment, post-treatment, and a follow-up 6 and 12 months after the end of treatment. Once the study has been explained and the informed consent has been signed, participants will be randomly assigned to one of two experimental conditions: 1) The adaptation of the FC protocol for relatives of ED-PD patients (FC: ED-PD) will be applied; 2) The Treatment as Usual Optimized Treatment (TAU-O) protocol will be applied. Randomization will be performed by an external researcher who will not participate in any of the phases of the project. The randomization sequence will be hidden from the evaluators participating in the study. The G*Power 3.1 software [44] will be used for this purpose. Assessment of participants will be carried out by a clinician other than the professional administering the treatments. Upon completion of the randomized controlled clinical trial, in-depth interviews will be conducted with family members who have successfully completed the intervention (e.g. clinically significant change) and with family members who drop out of the intervention. In all the potential groups, the aim will be to explore participants' experiences in order to learn about barriers and facilitators of the intervention.

### Sample size

To calculate the sample size, effect sizes found in previous studies on the topic have been considered. Grenyer et al. [30] tested a group psychoeducation protocol for caregivers of people with BPD in a controlled study that reports medium to large effect sizes (dyadic adjustment, *d* = 0.78; family empowerment, *d* = 1.4). Moreover, Grenyer obtained significant improvements on measures of illness burden between post-assessment and 12-month follow-up, with medium effects (*d* = 0.45). These effects are in line with the literature on psychological treatments for relatives of people with ED (Positive Caregiver Experience, *g* = -0.80) [14]. Given these data, an effect size of 0.50 is expected in the present study, adopting a conservative approach. Because our design includes two experimental conditions, t-tests are assumed for the statistical analyses. Considering an alpha of 0.05 and a statistical power of 0.80 in a two-tailed t-test, the total sample size needed to reach an effect size of 0.60 in loading is 90 participants (45 participants per experimental condition). To control for the maximum possible loss of subjects during treatment, based on the literature on previous programs for family members of BPD or ED patients, a dropout rate of 30% is expected [34–36]. Therefore, the required sample size should contain 124 participants in all (62 participants per group), as Fig. 1 shows. These calculations were carried out using the software program G*Power 3.1 [44].

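### The plan declares a conservative expected effect of 0.50 but sizes the trial for 0.60, so the stated 80% power does not apply to the effect it says it expects

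*Protocol article*

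**What the plan says.** Everything at issue is in one paragraph of the protocol article, under Methods, Sample size. After listing effects from earlier studies, the authors conclude that "an effect size of 0.50 is expected in the present study, adopting a conservative approach". They name the test used for sizing: "Because our design includes two experimental conditions, t-tests are assumed for the statistical analyses". The next sentence sets the error rates, "Considering an alpha of 0.05 and a statistical power of 0.80 in a two-tailed t-test", and gives the result: "the total sample size needed to reach an effect size of 0.60 in loading is 90 participants (45 participants per experimental condition").

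The paragraph then allows for attrition, stating that "a dropout rate of 30% is expected", and arrives at enrolment: "the required sample size should contain 124 participants in all (62 participants per group").

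Nothing in the paragraph, or elsewhere in the article, explains why the calculation uses 0.60 when the expected effect is 0.50. The word rendered as loading most naturally means caregiver burden, which is one of the primary outcomes for family members under Measures. That is an inference; the paragraph does not say so.

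**The concern.** A sample size rests on one design effect. Here two are stated, and they point in opposite directions. The smaller is presented as the cautious choice, while the larger, which gives a smaller trial, produces the number. A reader who takes the paragraph at face value will believe that the trial has 80% power for a cautiously chosen effect of 0.50.

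This matters when the result is interpreted. The trial is declared a superiority trial. If the difference is not significant, the weight given to that result depends on how likely the trial was to detect the effect the authors expected. A stated 80% implies a 20% chance of missing it. If the sizing test gives about 65%, that chance is about 35%.

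The unseen full protocol or analysis plan cannot settle this. The article does not omit a detail; it gives two incompatible values for the same quantity.

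**Working it through.** **Inputs, all from the Sample size section:** two-sided alpha 0.05; power 0.80; two-sample t-test; equal arms; effect size d = 0.60 (used) or 0.50 (declared as expected); dropout 30%; enrolment 62 per arm.

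**Step 1. Reproduce the plan's figure.** The normal approximation gives n per arm = 2(1.960 + 0.842)² / d² = 15.70 / d². At d = 0.60 this is 15.70 / 0.36 = 43.6, so 44. The exact noncentral-t calculation, which is the one G*Power makes for a t-test, gives 44.6, so 45 per arm and 90 in all. The stated figure is reproduced at d = 0.60.

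**Step 2. Check whether 0.50 could also give 90.** The normal approximation gives 15.70 / 0.25 = 62.8, so 63. The noncentral t gives 63.8, so 64 per arm and 128 in all. A one-sided test at d = 0.50 would still need 51 per arm, or 102. No reading of 0.50 leads to 90, so 0.60 is not a misprint for 0.50 in the calculation.

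**Step 3. Power at the declared effect.** The noncentrality parameter is d × √(n/2), with 2n − 2 degrees of freedom.

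| Evaluable per arm | Basis | Noncentrality at d = 0.50 | Power at d = 0.50 | Power at d = 0.60 |
|---|---|---|---|---|
| 45 | the plan's evaluable target | 0.50 × √22.5 = 2.372 | 65.0% | 80.4% |
| 43 | 62 × 0.70 = 43.4, rounded down | 0.50 × √21.5 = 2.318 | 63.0% | 78.5% |
| 62 | no outcome data lost | 0.50 × √31 = 2.784 | 78.9% | 91.2% |

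**Step 4. Read the result in terms of the effect.** For 80% power on the t-test, the detectable effect is 0.597 with 45 per arm, 0.611 with 43 and 0.507 with 62. Even with every enrolled participant analysed, the design falls just short of 80% power at 0.50.

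**The case against.** **Enrolling 124 covers the gap.** It does not. The paragraph assigns the whole excess over 90 to dropout. If there were no dropout at all, power at 0.50 would be 78.9%. That is close to 80%, and it is the fair upper end of the range on this test, but it requires that no outcome data be lost.

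**The t-test is not the trial's analysis.** This stands as a limit on the claim. The Data analyses section plans repeated-measures ANOVA and, for intention to treat, mixed-effects models with full-information maximum likelihood. A reader might infer that the trial will have only 65% power in its actual analysis. The documents do not support that. Use of baseline scores and partial data could raise power, and delivery of the programmes in groups could lower it. The article gives no correlation between baseline and outcome and no other figure from which either effect could be computed. The 65% is therefore the power of the plan's own sizing test. The plan's 80% is a figure for that same test, so the comparison between the two is like for like.

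**A trial may be sized for a target larger than the expected effect.** It may, if the target is stated and justified. The paragraph does neither, and its description of the approach as conservative says the opposite of what was done.

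**The cited burden effect.** A reader might infer from d = 0.45, the only burden effect cited, that even 0.50 is too optimistic. That does not follow. The article describes this value as "significant improvements on measures of illness burden between post-assessment and 12-month follow-up", which is a change over time. As described, it neither estimates nor bounds the difference between the two arms, so it can be used neither to support 0.50 or 0.60 nor to argue against them.

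**Conclusion.** The concern holds as an internal contradiction with a measurable consequence. The 90 evaluable participants come from d = 0.60, not from the declared expectation of 0.50. On the sizing t-test at two-sided alpha 0.05, power at 0.50 is about 65% for the evaluable number the plan relies on and about 63% after the plan's own 30% loss. It reaches about 79% only with no loss. The 80% claim is therefore wrong for the effect the plan says it expects, and right for 0.60 at 45 per arm.

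This rests on equal arms, independent observations and the two-sample t-test that the plan itself assumes. It does not show that the trial is too small for its mixed-model analysis, and it does not show which of 0.50 and 0.60 is the more plausible effect. The documents allow neither conclusion.

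**What to change.** Reconcile the two effect sizes in the Sample size paragraph, in one of two ways:

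- State that the trial has about 80% power for d = 0.60 with 45 evaluable per arm, give the rationale for 0.60, and remove the statement that a conservative 0.50 was used. Deleting 0.50 without justifying 0.60 would leave the design effect unsupported.
- Keep 0.50 as the expected effect and state that t-test power at that effect is about 63–65%.

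In either case, do not cite the effect of 0.45 from post-assessment to 12 months as evidence for or against a between-arm difference. Do not replace the 80% with a baseline-adjusted power figure that rests on an assumed correlation, since that would exchange one unsupported figure for another.

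The cost is a few sentences and, under the second option, a less favourable stated power. Enrolment does not change. For scale, 80% power at 0.50 on the t-test would need 128 evaluable, and 128 / 0.70 = 182.9, or 184 enrolled with equal arms, against the planned 124. The Data Availability section indicates that recruitment is already under way, and this point does not ask for resizing.

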### Interventions

#### Family connections for relatives of people with eating disorders and personality disorders (FC: ED-PD)

The intervention lasts three months and includes 12 sessions with a weekly two-hour group format. The FC program [34]) is divided into six modules, but the research team developed the program adapted to ED and PD in seven modules, which are described below [34]:Module 1Presentation of the program, objectives, structure, tasks, etc. Up-to-date information and research on ED and PD (Epidemiology, frequency, Risk factors, and protective factors).Module 2 Psychoeducation on the development of ED and PD, explanatory theories, available treatments, and comorbidity with PD.Module 3 Emotional regulation skills, skills of acceptance, validation, approach, and awareness, and to decrease emotional reactivity.Module 4 Skills to improve the quality of relationships in family interactions (letting go of guilt and anger, acceptance skills in relationships).Module 5Communication skills and effective self-expression.Module 6 Problem management and making safe plans for crisis management.

All the modules include practice exercises, video viewing, and homework assignments. In addition, throughout the program, with the goal of increasing social support, the FC program provides a forum where participants can stay in touch and share common problems and solutions.

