### Data analyses

Regarding data analysis, the results of the pilot feasibility study using focus groups will be analyzed using thematic analysis in order to identify the topics that emerge from the focus groups [72]. Data reporting will be carried out following the COREQ guidelines [73]. In addition, qualitative research quality criteria recently developed by Levitt et al. [74] will be pursued in order to achieve what the authors refer to as methodological integrity in the qualitative field.

In the controlled clinical trial, the CONSORT guidelines [43] will be followed. First, participants' scores in the two conditions will be compared before the intervention to check that there are no significant differences between them on the outcome measures and that they are, therefore, comparable after randomization. ANOVAs will be conducted for continuous variables and Chi-square tests for categorical variables. For outcome measures at post-treatment, we will study whether the assumption of homoscedasticity is met with Levene's test. If this assumption is met, repeated-measures ANOVAs and F-tests will be used to compare the two experimental conditions. If the homoscedasticity assumption is not met, the Brown-Forsythe test will be applied. F-tests for statistical significance will be followed by post hoc comparisons. In particular, Tukey will be used when the homoscedasticity assumption is met, and Games-Howell if the homoscedasticity assumption is not met. Appropriate analyses will also be carried out to calculate intervention effect sizes and confidence intervals. The intention-to-treat principle will be used when analyzing pre- and post-treatment data and at 12-month follow-up, using mixed-effects models with full information and maximum likelihood estimation. To complement the results of ANOVAs and post hoc comparisons, effect sizes will be calculated using the standardized mean difference proposed by Cohen [75]. These effect sizes will be calculated to assess changes within and between groups, all based on a pooled standard deviation.

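### FC: ED-PD is delivered in groups, but the sample size and the ANOVA comparisons treat relatives as independent; if outcomes correlate within FC groups, standard errors are too small and power is overstated

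*Protocol article*

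**What the plan says.** All references are to the protocol article.

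- **Procedure:** each family member is assigned individually to FC: ED-PD or TAU-O.
- **Interventions, FC: ED-PD:** the programme "includes 12 sessions with a weekly two-hour group format". In addition, "the FC program provides a forum where participants can stay in touch and share common problems and solutions".
- **Interventions, TAU-O:** usual care at the referral centre continues, with one added three-hour group session.
- **Sample size:** "Because our design includes two experimental conditions, t-tests are assumed for the statistical analyses". The calculation is framed as "Considering an alpha of 0.05 and a statistical power of 0.80 in a two-tailed t-test" and gives 90 relatives, 45 per arm, at an effect size of 0.60. The only inflation is for loss of participants ("a dropout rate of 30% is expected"), which leads to a target of 124, or 62 per arm. No group size, number of groups, ICC or design effect appears.
- **Data analyses:** if variances are homogeneous, "repeated-measures ANOVAs and F-tests will be used to compare the two experimental conditions"; otherwise Brown-Forsythe is used. Neither is described with a therapy-group term. Mixed-effects models with maximum likelihood are also named, as the way to apply the intention-to-treat principle.

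**The concern.** Relatives in one FC group spend 12 two-hour sessions together, 24 hours in all, and mutual support is part of the treatment. Their outcomes may therefore be more alike than those of relatives in different groups. TAU-O adds only three shared hours. This is a partially nested design: individual randomisation, with clustering created after randomisation, mainly in one arm.

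A t-test or ANOVA that treats every relative as an independent observation ignores the between-group variance in the FC arm. With a positive ICC, the test rejects a true null hypothesis too often, its confidence intervals are too narrow, and a sample size built on it promises more power than a valid test delivers. In a superiority trial, false rejections include false claims that FC: ED-PD works.

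**Working it through.** **1. The plan's own figure.** Inputs from the Sample size section: two-sided alpha 0.05, power 0.80, effect size 0.60, equal arms. The exact noncentral t calculation gives 45 per arm with power 0.804 (44 per arm gives 0.795). The stated 45 therefore reproduces under independence, and no allowance for clustering is hidden in it. Nor does the 124 contain one: the text attributes the increase to dropout alone, and 124 × 0.70 = 86.8, already below 90.

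**2. Assumptions, because the article gives no figures.**
- FC groups start with 8 to 10 relatives. With 62 randomised to FC, that is 62/10 = 6.2 to 62/8 = 7.75 groups.
- 45 are analysed in each arm, so the analysed group size m is 45/7.75 = 5.8 to 45/6.2 = 7.3.
- TAU-O is unclustered, and total outcome variance is equal in the two arms.
- ICC is 0.01 to 0.10.
- The illustration is a single post-treatment comparison of two means.

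**3. Formulas.**
- Design effect in FC: DE = 1 + (m − 1) × ICC.
- Variance ratio of the arm difference, true to assumed: r = (DE + 1)/2.
- Actual error of the unadjusted test: 2 × [1 − Φ(1.96/√r)].
- Power of a correctly sized test: noncentral t with noncentrality 0.60 × √(45/2)/√r = 2.846/√r, first with the plan's 88 degrees of freedom.

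**4. Results.**

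| ICC | m | DE | r | Actual error | Power |
|---|---|---|---|---|---|
| 0 | any | 1.00 | 1.00 | 5.0% | 80.4% |
| 0.01 | 5.8 | 1.05 | 1.02 | 5.3% | 79% |
| 0.02 | 7.3 | 1.13 | 1.06 | 5.7% | 78% |
| 0.05 | 5.8 | 1.24 | 1.12 | 6.4% | 76% |
| 0.10 | 7.3 | 1.63 | 1.31 | 8.7% | 69% |

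For the ICC 0.05 row: DE = 1 + 4.8 × 0.05 = 1.24; r = 2.24/2 = 1.12; √r = 1.058; 1.96/1.058 = 1.852, which gives 6.4%.

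**5. Few groups.** With k FC groups, approximate Satterthwaite degrees of freedom are (DE + 1)²/[DE²/(k − 1) + 1/44].
- ICC 0.05, k = 7.75: 5.018/(0.228 + 0.023) ≈ 20, and power falls from 76% to about 73%.
- ICC 0.10, k = 6.2: 6.896/(0.508 + 0.023) ≈ 13, and power falls from 69% to about 63%.

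**The case against.** **The size is unknown.** Group size, number of groups and ICC appear nowhere in the article, and nothing in it favours an ICC of 0.05 to 0.10 over 0.01 to 0.02. This stands. The direction is fixed for any positive ICC, but the size is only a range, and at its low end the loss is one or two points of power.

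**The mixed-effects model may already deal with it.** A reader might infer that this model also ignores therapy groups. The article does not support that. It leaves the random-effects structure unstated, as an article may when the full protocol or analysis plan is not shown. The point rests on the t-test and the ANOVA or Brown-Forsythe comparisons, which are stated. The mixed-model sentence does not repair these, because the ANOVAs remain a named comparison of the arms and the sample size is unaffected.

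**Larger figures are tempting.** Full groups of 8 to 10 among 45 analysed relatives would give variance increases of 18% to 45%, error of about 7% to 10%, and power of about 74% to 65%. But that implies only 4.5 to 5.6 groups, which does not fit 62 relatives randomised to groups of that size.

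**Some sources of clustering are not stated.** The article does not say that each FC group has its own therapist or its own forum, or that TAU-O relatives share nothing beyond their session. The shared weekly sessions are stated and are enough for the point. An unclustered TAU-O arm is an assumption; clustering there would make matters worse.

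**Another problem in the same section may matter more.** The text says that "an effect size of 0.50 is expected in the present study" but sizes on 0.60. At 0.50, 45 per arm gives power of 0.65 with no clustering at all. That is a separate point and does not remove this one.

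**Conclusion.** The point holds conditionally. As written, the sample size and the ANOVA or Brown-Forsythe comparisons assume independence that the group delivery of FC: ED-PD puts in doubt. If the within-group ICC is positive, standard errors are too small and the stated 80% power at 0.60 is too high.

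Under the assumptions listed, an ICC of 0.05 to 0.10 means about 12% to 31% more variance, true error of about 6.4% to 8.7%, and power of about 76% to 69%, with a further loss from the small number of groups. An ICC of 0.01 to 0.02 means error of about 5.3% to 5.7% and power of 78% to 79%.

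A reader might conclude that the standard errors are certainly and badly wrong. The article does not show that, because it gives neither ICC nor group size. The change should still be made: the defect bears on the validity of the main comparison and is cheap to correct.

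**What to change.** - Record therapy-group membership for every relative. The Data Availability section says recruitment is still under way, so this can be done before analysis.
- Make the mixed-effects model already named in Data analyses the between-arm analysis, in place of the ANOVAs. Include a random intercept for therapy group in the FC arm, treat TAU-O relatives as unclustered, and use Satterthwaite or Kenward-Roger degrees of freedom. Add a sensitivity analysis that clusters TAU-O relatives by their group session.
- Restate the power paragraph with the planned group size, the expected number of FC groups and a range of ICCs.

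**Cost:** one extra variable and one random effect. Intervals become wider, and the stated power may fall clearly below 80%. Restating the power needs no extra participants; restoring it to 80% would.
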